## Abstract

**Background:**

Mild cognitive impairment (MCI) is an intermediary condition between typical cognitive decline that occurs owing to aging and dementia. It is necessary to implement an intervention to slow the progression from MCI to Alzheimer’s disease. This manuscript reports the protocol for a clinical trial on the effect of acupuncture in patients with MCI.

**Methods:**

The trial will be a randomized, prospective, parallel-arm, active-controlled trial. Sixty-four patients with MCI will be randomized to the Rehacom or acupuncture group (*n* = 32 each). The participants in the acupuncture group will receive electroacupuncture at GV24 (Shenting) and GV20 (Baihui) and acupuncture at EX-HN1 (Sishencong) once (30 min) a day, twice per week for 12 weeks. The patients in the Rehacom group will receive computerized cognitive rehabilitation using RehaCom software once (30 min) daily, twice weekly for 12 weeks. The primary outcome measure is the change in the Montreal Cognitive Assessment Scale score. The secondary outcome measures are the Geriatric Depression Scale, Alzheimer’s Disease Assessment Scale-Korean version-cognitive subscale-3 scores, and European Quality of Life Five Dimensions Five Level Scale. The safety outcomes will include the incidence of adverse events, blood pressure, blood chemistry parameters, and pulse rate. The efficacy outcome will be assessed at baseline and at six weeks, 13 weeks, and 24 weeks after baseline.

**Discussion:**

The findings of this protocol will provide information regarding the effects of acupuncture on MCI.

**Clinical trial registration:**

https://cris.nih.go.kr/cris/search/detailSearch.do?search_lang=E&focus=reset_12&search_page=M&pageSize=10&page=undefined&seq=25579&status=5&seq_group=25579, KCT0008861.

## Introduction

1

Mild cognitive impairment (MCI), an intermediary condition between typical cognitive decline owing to aging and dementia, is a slight impairment in memory or other cognitive domains. MCI has no significant effects on daily living and does not meet the diagnostic criteria for Alzheimer’s disease (AD) (1, 2). In China, the prevalence of MCI increases with age from 11.9% in the 60s to 33.1% in the 90s or older (3). MCI in older adults is at a higher risk of progressing to AD (4). A previous five-year follow-up study reported that the annual conversion rates to dementia among older Chinese adults were 6.3 and 1.6% at baseline for participants with MCI and normal cognitive ability, respectively (5). The cognitive ability of patients with MCI may stabilize or return to normal status; however, progression to AD is more common. The annual incidence rates of MCI and dementia were reported to be 4.1 and 5.17%, respectively, in a previous cohort study. Notably, the rate of conversion to probable AD is high in the United States (241.3/1000 person-years), and MCI reverts to normal cognition in only few cases (6). AD is an irreversible condition; thus, early detection of MCI and the prevention of its progression may be urgent and important in the management of AD (7).

The demand for effective interventions for treating MCI is growing; however, no drugs supported by high-quality evidence have been recommended for treating MCI (8). Nevertheless, new management measures, such as regular exercise, cognitive training, and the management of modifiable risk factors, may aid in effectively managing MCI (9, 10).

Acupuncture, a technique involving the application of manual and electrical stimulation after inserting needles into acupoints, has been used for treating cognitive decline, including MCI (11, 12). The therapeutic effects of acupuncture on MCI have been reported in several systematic reviews and meta-analyses. Acupuncture was safe and effective for MCI when used as an alternative or adjunctive treatment compared with that observed when sham acupuncture, medication, and usual care were used as treatment (12–16). A systematic review of neuroimaging studies revealed that acupuncture may have an effect on the regulation of the central executive network, salience network, and default mode network, especially in the prefrontal cortex, cingulate cortex, and hippocampus in patients with MCI (17). Moreover, acupuncture was found to have modulatory effects on various regions of the brain in patients with MCI in a regional homogeneity-based meta-analysis (18). The potential therapeutic mechanisms of acupuncture include the restoration of the blood–brain barrier, downregulation of Aβ accumulation and tau protein phosphorylation, enhancement of synaptic plasticity, reduction of neuroinflammation, improvement of mitochondrial activity, and reduction of neuronal apoptosis (19). In a network meta-analysis that compared the efficacy of nine interventions for MCI, acupuncture and music therapy were found to have improved cognitive function in patients with MCI; thus, these treatment options may be favored for treating MCI (20).

Several studies have been conducted on the efficacy of acupuncture for MCI; however, the methodological quality of these studies has been insufficient in providing convincing evidence (12–18). Our manuscript describes the protocol for a rigorously designed clinical study that aims to explore the effects of acupuncture on MCI. The findings of this trial will provide evidence regarding the efficacy of acupuncture for MCI.

## Methods and analysis

2

### Objective

2.1

We intend to investigate the efficacy of acupuncture for MCI by comparing its effect on cognitive improvement with that of computerized cognitive rehabilitation (CCR).We intend to evaluate the ability of acupuncture to improve the quality of life, memory, and depressive symptoms in patients with MCI.We also intend to explore the safety of acupuncture in patients with MCI.

### Hypothesis

2.2

The acupuncture group compared with the control group will show a better effect in improving cognitive ability.Significant improvement in quality of life, memory, and depressive symptoms will be observed in the acupuncture group.EA is a safe therapy for patients with MCI.

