#### Efficacy outcome

2.13.1

The primary outcome measure is the between-group difference in changes in MoCA-K scores 13 weeks after baseline. The secondary outcome measures of this study are (1) the between-group differences in changes in the MoCA-K scores 6 weeks after baseline; (2) the between-group differences in changes in the MoCA-K scores 24 weeks after baseline, and (3) the changes in the GDS, Alzheimer’s Disease Assessment Scale-cognitive subscale-3 (ADAS-K-cog 3), and European Quality of Life Five Dimension Five Level scale (EQ-5D-5L) scores 6, 13, and 24 weeks from baseline.

MoCA, a screening instrument that is widely used to detect MCI, is used to measure the changes in cognitive function. It is a 30-point test that can evaluate the cognitive domains of orientation to place and time, visuospatial/executive function, short-term memory recall, concentration, attention, working memory, and language (26, 27).

ADAS-K-cog 3 is used to evaluate memory. It includes three tasks of the ADAS-K-cog 11 (orientation, word recall, and word recognition), which demonstrate no ceiling effects in MCI (28).

GDS is used to identify depression as it can distinguish between the symptoms of depression and dementia in elderly people. This is a widely used screening instrument for evaluating depressive symptoms in elderly individuals (29).

EQ-5D-5L is a commonly used health utility instrument to explore quality of life (30). The quality weight of EQ-5D-5L was based on a previous study (31).

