### Statistical analysis

2.17

An independent statistician will analyze the final data using SPSS software (version 21.0, IBM). A full analysis set will be conducted to assess the efficacy of the treatment, and missing data will be inputted using the last observation carried forward method. The significance level will be set at 5% (two-tailed). Categorical variables will be expressed as percentages or frequencies, whereas continuous variables will be expressed as mean and standard deviation or median with an interquartile range. Interim analysis will not be performed.

Friedman test or a one-way repeated-measures analysis of variance for intragroup comparisons and analysis of covariance, as well as an independent *t*-test or Mann–Whitney U test will be used for intergroup comparisons to analyze the changes in efficacy outcomes. Sub-analyses will be conducted according to age (under 70 and over 70 years old).

The occurrence of AEs between the two groups will be compared using the chi-square test or Fisher’s exact test. The Mann–Whitney U test or independent *t*-test will be used for intergroup comparisons to analyze the changes in blood chemistry parameters, blood pressure, and pulse rate.

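### The quality-of-life, memory and depression hypothesis is worded as improvement within the acupuncture arm and is not tied to the planned between-group test, so a before-after p-value could confirm it

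*Protocol article*

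**What the plan says.** The Hypothesis section (2.2) treats two sets of outcomes differently. For cognition it is comparative: "The acupuncture group compared with the control group will show a better effect in improving cognitive ability". For the remaining outcomes it is not: "Significant improvement in quality of life, memory, and depressive symptoms will be observed in the acupuncture group".

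The Objective section (2.1) shows the same split. Cognition is to be studied against CCR. The other outcomes are introduced with "We intend to evaluate the ability of acupuncture to improve the quality of life, memory, and depressive symptoms in patients with MCI", again without a comparator.

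Under Efficacy outcome (2.13.1) the primary endpoint is explicit: "The primary outcome measure is the between-group difference in changes in MoCA-K scores 13 weeks after baseline". Secondary items (1) and (2), MoCA-K at 6 and 24 weeks, are also between-group differences. The third item is worded only as "3) the changes in the GDS", and continues in the same way for ADAS-K-cog 3 and EQ-5D-5L.

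Statistical analysis (2.17) plans both kinds of test in one sentence. It begins with "Friedman test or a one-way repeated-measures analysis of variance for intragroup comparisons" and goes on to ANCOVA, the independent t-test or the Mann–Whitney U test, which "will be used for intergroup comparisons to analyze the changes in efficacy outcomes". It does not assign either kind to a particular hypothesis.

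**The concern.** A within-arm test asks whether scores moved from baseline. It makes no use of the randomisation, so it cannot separate an effect of acupuncture from anything else that moves scores over 24 weeks. The protocol contains several candidates:

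- ADAS-K-cog 3, the memory measure, is given four times according to Table 1, so practice is possible.
- Both arms receive education on exercise and self-management.
- Participants are not among those listed as blinded, and needling cannot be mistaken for computer training. GDS and EQ-5D-5L are therefore open to attention and expectation.

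If the second hypothesis is judged on its literal wording, the trial could report that acupuncture significantly improved memory, mood and quality of life when it did no better than CCR. The primary endpoint is not affected.

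**Working it through.** **Step 1: wording side by side.**

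| Place | MoCA-K / cognition | GDS, ADAS-K-cog 3, EQ-5D-5L |
|---|---|---|
| Objective 2.1 | compared with CCR | no comparator |
| Hypothesis 2.2 | versus control group | improvement in acupuncture group |
| Efficacy outcome 2.13.1 | between-group difference | change |
| Statistical analysis 2.17 | within- and between-group tests | within- and between-group tests |

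The comparator is missing in all three places where these outcomes are defined. In the fourth, a valid comparison is planned but not designated as the deciding one.

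**Step 2: sample sizes used.** The plan gives no figure for these outcomes, so only n and alpha are taken from it. Its own arithmetic reproduces: 8 × 0.79 × 0.21 / 0.221² = 27.2, reported as 27 per group; 27 / 0.85 = 31.8, rounded up to 32. Alpha is 0.05 two-sided. Whether that formula is adequate is a separate matter.

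**Step 3: chance that a within-arm test is significant with no acupuncture effect.** Let d be a shift common to both arms, in SDs of change. The documents give no value for d, so a range is assumed. For a two-sided paired t-test, power = P(|T| > t(0.975, n−1)), where T is noncentral t with n−1 degrees of freedom and noncentrality d√n. The critical value is 2.040 for n = 32 and 2.056 for n = 27.

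| d | d√32 | significant, n = 32 | d√27 | significant, n = 27 |
|---|---|---|---|---|
| 0 | 0 | 5.0% | 0 | 5.0% |
| 0.2 | 1.131 | 19.5% | 1.039 | 17.0% |
| 0.3 | 1.697 | 37.6% | 1.559 | 32.4% |
| 0.5 | 2.828 | 78.2% | 2.598 | 70.6% |

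**Step 4: the planned within-group test.** The paired t-test is a stand-in, since the protocol names a one-way repeated-measures ANOVA or the Friedman test. The ANOVA was simulated (10,000 trials per case) over four visits, with compound symmetry, correlation 0.5 and the same shift d at every follow-up. It was significant in 18.0%, 36.6% and 82.3% of trials at d = 0.2, 0.3 and 0.5 with n = 32, and in 15.2%, 31.6% and 74.9% with n = 27. The picture is the same.

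**Step 5: the between-group test.** A two-sample t-test on change, simulated with the same shared shifts (20,000 trials per case), was significant in 4.9% to 5.3% of trials throughout. A shift common to both arms cancels in the comparison.

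**The case against.** The strongest reply is that the same sentence of section 2.17 that plans the within-group tests also plans between-group tests of changes in efficacy outcomes, and GDS, ADAS-K-cog 3 and EQ-5D-5L are listed as efficacy outcomes. The trial is randomised and active-controlled, and the neighbouring hypothesis is comparative. The one-arm wording may be shorthand in a condensed article, and the deciding test for each secondary outcome may be set in a statistical analysis plan that is not shown. The first part stands: a valid comparison will exist, and a reader who infers that these outcomes get within-arm analysis only would be wrong. It does not remove the point. The hypothesis is stated in the article, and an analysis plan that decided it by a between-group test would be answering a different hypothesis from the published one.

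Other strong readings are also not supported:

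- *That improvement in one arm is to be expected regardless.* The documents show ways it could happen, not that it will. They also describe MCI as slowly progressive, which works the other way.
- *That regression to the mean will produce improvement.* Entry is restricted on K-MMSE and MoCA-K, so any effect on ADAS-K-cog 3 is indirect. For GDS, entry is capped at 18, and selecting low scores would push later scores towards worse depression.
- *That every outcome is tested five times.* That is true of MoCA-K and GDS; ADAS-K-cog 3 and EQ-5D-5L are given four times.
- *That the arms will be contrasted by which one reaches significance.* The protocol states no such rule, so no error rate for it is claimed here.

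**Conclusion.** The point holds in this limited form: the second hypothesis and secondary outcome (3) omit the comparison with CCR, and the analysis section does not tie them to the between-group test that it already plans. The hypothesis as worded can therefore be confirmed without using the control arm. It concerns secondary outcomes only.

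The size depends on a nonspecific shift that the documents do not give. Over an assumed 0.2 to 0.5 SD of change, false confirmation per outcome runs from about 15% to 82%, depending on the test and on whether 27 or 32 patients are analysed, against about 5% for the between-group test. With no shift, the within-arm test is also at 5%. These figures assume normal changes, the same shift in both arms and no acupuncture effect. They show what the wording permits; they do not predict the trial's result.

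**What to change.** Reword the second hypothesis, and the matching objective, as a between-group difference in change versus CCR. Define item (3) in the same terms as items (1) and (2). State in section 2.17 that any efficacy conclusion on GDS, ADAS-K-cog 3 and EQ-5D-5L rests on the between-group analysis, preferably ANCOVA adjusted for baseline since it is already listed. Label the Friedman and repeated-measures results descriptive, with no efficacy claim drawn from them.

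This needs no extra patients, visits or data. The costs are that within-arm p-values can no longer support a claim, and that the revision needs IRB approval, as Quality control (2.15) requires. Because the control is active, a null between-group result would not show that acupuncture has no effect, but a before-after test does not solve that either. A Holm adjustment across the three outcomes and a single claim time point are optional and not part of this correction.

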**Figure 1 fig1:**
[figure not shown]
Flow chart of this study.

### Participant recruitment

2.4

Recruitment will be conducted at the Dongshin University Gwangju Korean Medicine Hospital, Republic of Korea, using local newspaper advertisements, community posters, and advertisements on the Internet. Potentially eligible individuals will receive an explanation regarding the aims and objectives of the trial from the investigator and clinical research coordinator (CRC). Only the participants who voluntarily sign the informed consent form before participation will be included in the trial. Patients will be screened using the inclusion and exclusion criteria. The CRC will explain the schedule of the next visit at each visit and adjust the schedules to ensure compliance with the protocols.

### Inclusion

2.5

(1) Elderly adults aged between 55–85 years, (2) patients with memory problems persisting for at least three months who meet the diagnostic criteria for MCI (22), (3) patients with a Global Deterioration Scale score of 2 or 3, (4) patients with a Korean Mini-Mental State Examination score of 20–23, (5) patients with a Korean version of Montreal Cognitive Assessment scale (MoCA-K) score of 0–22, (6) patients with a Geriatric Depression Scale (GDS) score of 0–18, (7) patients with at least six years of education or adequate proficiency in Korean language to facilitate reliable study assessments, and (8) patients who are capable of providing informed consent voluntarily.

### Exclusion criteria

2.6

(1) Diagnosis of vascular dementia in accordance with the NINDS-AIREN criteria or diagnosis of AD according to the NINCDS-ADRDA criteria; (2) a history of structural brain diseases that could result in cognitive disorder, such as congenital mental retardation, intracranial space-occupying lesions, traumatic brain injury, or stroke; (3) a history of serious illness, such as Huntington disease, Parkinson’s disease, cancer, central nervous system, liver, cardiovascular, and kidney diseases, and multiple sclerosis; (4) a history of neurological disease within the preceding 12 months confirmed using brain magnetic resonance imaging or computed tomography; (5) a history of alcohol, drug abuse, or mental illness (depression, serious anxiety, or schizophrenia) within six months prior to screening; (6) currently receiving treatment for MCI, such as Korean medicine treatment, drug, or cognitive training within 4 weeks prior to screening; (7) difficulties with outcome measures due to visual and hearing impairments; (8) unfit to receive EA owing to the presence of blood-clotting abnormalities, such as scalp infection, the presence of a pacemaker, or hemophilia; (9) pregnancy or breastfeeding; (10) participation in another study within 8 weeks prior to screening or current participation in another study.

### Dropout and violation criteria

2.7

Dropout criteria: (1) incidence of any serious adverse event (SAE), (2) incomplete data that could impact the results, (3) withdrawal of consent for participation, or (4) exclusion from the study deemed necessary by the Institutional Review Board (IRB) or principal investigator (PI).

Exclusion from the per-protocol set analysis will be mandated for participants who demonstrate (1) remarkable protocol violation or serious deviation in protocol implementation and (2) an intervention compliance rate of <75% (completed less than 18 of the 24 scheduled intervention sessions).

### Randomization

2.8

The participants will be randomized to the Rehacom or acupuncture group (*n* = 32 each) after a screening visit in accordance with random numbers generated using SPSS (version 21.0; IBM). The random code will be sealed in an opaque envelope and stored in a cabinet with a double lock.

### Implementation

2.9

Allocation and random number generation will be conducted by an independent investigator who is not involved in this study. The enrollment procedures will be performed by the CRC.

### Blinding

2.10

Statisticians, assessors, and data analysts will be blinded to the allocation during the trial process. Unblinding will be permitted with the approval of the IRB if SAEs occur. Only investigators with no conflicts of interest will be involved in the trial to avoid bias. All researchers will be trained in blinding procedures prior to participation.

### Interventions

2.11

#### Acupuncture treatment

2.11.1

Acupuncture treatment will be provided by licensed Korean medical doctors. The physicians will use the same technique to ensure compliance with this protocol. We adopted the acupuncture treatment methods, including the stimulation parameters of EA, based on those used in our preliminary study and acupuncture clinical studies for MCI (13, 16, 23, 24). The participants in the acupuncture group will receive electroacupuncture (EA) at GV24 (Shenting) and GV20 (Baihui), along with acupuncture at EX-HN1 (Sishencong). Single-use sterile acupuncture needles (DB106; size, 0.25 × 30 mm; Dongbang Medical Co., Ltd., Seongnam, Republic of Korea) and an EA stimulator (STN-330; Stratek, Co., Ltd., Anyang, Republic of Korea) will be used in the trial. In the supine position, the anterior EX-HN1, GV20 (Baihui), and GV24 (Shenting) will be punctured in the anterior direction. The right, posterior, and left EX-HN1 (Sishencong) will be punctured in the direction of GV20 (Baihui). After the acupuncture needles are inserted, they will be retained in the acupoints for 30 min without manual stimulation. EA will be applied at GV24 (Shenting) and GV20 (Baihui) using the following parameters: voltage, 0–5 V; frequency, 3 Hz; and continuous waves. Participants in the acupuncture group will receive 24 sessions of acupuncture twice weekly for 12 weeks, with each session lasting for 30 min.

### Computerized cognitive rehabilitation treatment

2.12

Patients in the Rehacom group will receive CCR treatment in the seated position using RehaCom software. Rehacom consists of a large screen and an input panel that is used to train elderly individuals in several cognitive domains, including attention, verbal memory, delayed and episodic memory, and processing speed, as well as executive functions. All participants will receive training on the same tasks for equal durations (min/task) in each session. The training will be initiated at the beginner level of the training task, and the difficulty levels will be adjusted to meet the participant’s ability (23, 25). Participants in the CCR group will receive 24 sessions of CCR twice weekly for 12 weeks, with each session lasting for 30 min.

Management of modifiable risk factors, such as smoking, diabetes, hypertension dyslipidemia, cerebrovascular and heart disease, lower education level, regular exercise, rural residential status, and independent living, can be effective in the improvement of cognitive function in patients with MCI (3, 10). Therefore, all patients will be educated on self-management and exercise techniques. The CRC will monitor the participants’ medical condition at each visit, and the visit schedule will be changed in accordance with the participants’ request or the judgement of the PI to increase compliance with the study protocol. All participants will continue using currently received medications and treatments that do not affect their cognitive function during the trial. However, the participants will not be permitted to receive other treatments to improve the symptoms of MCI.

